## Materials and methods

Study design and setting

The present study has two phases. Phase one involves a comparative assessment between children with VI and normally sighted children. Phase two is a two-group parallel, randomized waitlist-controlled trial with a 1:1 allocation ratio to investigate the impact of a 12-week yoga intervention on lung function and other factors among children with VI (Figure 1).

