Posture assessment		X	X
Heart rate variability		X	X
Upper extremity muscle strength		X	X
Depression		X	X
Barriers to PA		X	-
Functional performance		X	-

**Table 4 TAB4:** Phase two trial schedule. T0 = enrollment of children with visual impairment from phase one; T1 = intervention to the yoga group for three months; T2 = post-assessment of both groups; T3 = intervention to the control group

Phase two				
Study time points	Enrollment	Intervention	Post-assessment	Intervention
	T0	T1	T2	T3
		Yoga group	Yoga and control group	Control group
Eligibility screening	X	-	-	-
Intervention		X	-	X
Assessments	-	-	-	-
Anthropometric details			X	
Lung function			X	
Posture assessment			X	
Heart rate variability			X	
Upper extremity muscle strength			X	
Depression			X	
Functional performance			X	

Phase two

The outcome measures for the RCT study will encompass lung function, posture assessment, heart rate variability, upper extremity muscle strength, and depression, utilizing the same tools employed before and after 12 weeks of intervention. Functional performance will be evaluated using the 6-Minute Walk Test (6-MWT).

Sample size

Based on an earlier study, the sample size was calculated using GPower software based on PEFR data, with an alpha of 0.05, power of 0.80, and an effect size of 0.8. A 20% attrition rate was incorporated to account for potential dropouts during the three-month yoga intervention in children with VI, who may experience health or participation-related challenges [19].

Recruitment

Participants will be identified by reaching out to special school administrators and teachers. An announcement will be made in the schools to raise awareness about the study and encourage participation. Additionally, teachers and supporting staff will be encouraged to spread the word within school networks. Parents or guardians will also receive information about the study orally during parent-teacher conferences. Recruitment and enrollment of participants will be performed by the study investigator.

Randomization and blinding

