## Results

Descriptive statistics will be used to summarise participants’ sociodemographic details at baseline. Categorical data will be analysed using the chi-square test to determine any significant associations. The normality of the data will be assessed using the Shapiro-Wilk test, while Levene’s test will be applied to ensure the equivalence of variances. To compare outcomes between the VI and normal-sighted groups, either an independent samples t-test or a Wilcoxon rank-sum test will be employed, depending upon the normality of the data. Correlational analysis will be conducted to identify associations between lung function and other outcomes. In phase two, the intervention group will be compared against the control group for all primary and secondary outcomes. We will choose the appropriate parametric or non-parametric test based on the normality of the data. The missing data will be substituted using the predictive mean matching (PMM) imputation method. Analysis will be performed using SPSS version 21 (IBM Corp., Armonk, NY, USA) or RStudio. The study is registered with CTRI and has received Ethics Committee approval in mid-calendar year 2023.

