This study combines objective health measures, such as lung function, muscle strength, posture, and heart rate variability, with validated psychological assessments, providing a comprehensive evaluation of children’s health. The RCT design, including a waitlist control group, allows all participants to benefit from the yoga program while providing a rigorous and ethically responsible evaluation of its effects. Inclusion of both visually impaired and sighted children allows meaningful comparisons and identification of specific needs in the VI population. Additionally, the structured 12-week yoga intervention with standardized protocols supports reproducibility and potential scalability for rehabilitation programs. Despite the robust design, several limitations should be acknowledged. Key limitations of the study include the open trial design, which may introduce performance and reporting bias as participants are aware of group allocation and may respond in socially desirable ways, and observer bias as assessors cannot be fully blinded. Variations in social support among participants are not controlled for, which could influence outcomes. Dropouts and missing data may also affect internal validity, though strategies such as imputation are planned to minimize their impact. Although participants come from different regions of the state, the study is conducted at a single center, which may limit generalizability to other regions.

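### Read literally, the missing-data rule is a single predictive mean matching fill; run that way in phase two, it understates standard errors at the attrition the plan allows for

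*Protocol article*

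**What the plan says.** The rule is one sentence in the statistical paragraph (Results section): "The missing data will be substituted using the predictive mean matching (PMM) imputation method". Just before it, on the phase two comparison, the same paragraph says "We will choose the appropriate parametric or non-parametric test based on the normality of the data". For the phase one comparison, the paragraph names the candidate tests as an independent-samples t-test or a Wilcoxon rank-sum test.

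The Sample size section sets the scale of missing data: "A 20% attrition rate was incorporated to account for potential dropouts during the three-month yoga intervention in children with VI". Strengths and limitations returns to the subject: "Dropouts and missing data may also affect internal validity, though strategies such as imputation are planned to minimize their impact".

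None of these places says how many completed datasets will be made, how results will be combined, or which variables enter the imputation model.

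**The concern.** Predictive mean matching fills a gap with the observed value of a child whose predicted outcome is similar. Done once, it gives a dataset of full size in which some values are copies of others. An ordinary t-test on that dataset uses the full number of children and ignores the uncertainty about the filled values. Its standard error is then too small, its interval too narrow and its false-positive rate above the nominal level.

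The wording points towards this use. Substituting values, checking normality and then choosing a t-test or rank-sum test is a sequence that runs as written on one completed dataset. On several datasets it does not: the normality check could select different tests in different datasets, and the rank-sum test has no standard pooling under Rubin's rules. At stake are the phase two comparisons with missing values, including the primary outcomes FVC, FEV1 and PEFR.

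**Working it through.** **Inputs from the article.** Alpha, power and effect size: "with an alpha of 0.05, power of 0.80, and an effect size of 0.8" (Sample size). Attrition allowance: 20% (Sample size). Allocation: "randomized waitlist-controlled trial with a 1:1 allocation ratio" (Study design and setting).

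**Assumptions.** The article gives no sample size, so there is no figure to reproduce. The test is taken as two-sided, missingness as completely at random, and the baseline-outcome correlation as 0 to 0.8.

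**Step 1: implied size.** Normal formula: n = 2(1.96 + 0.84)²/0.8² = 24.5, so 25 per arm. The t-based solution is 25.5, so 26 per arm. Allowing for dropout, 26/(1 − 0.20) = 32.5, so 33 per arm. Missing: 0.20 × 33 = 6.6, taken as 7, which leaves 26 observed.

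**Step 2: hand check with an uninformative baseline.** Outcome SD is 1.

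- A single-fill test reports about √(2/33) = 0.246.
- Complete cases have √(2/26) = 0.277.
- Filling 7 gaps with random observed values adds noise. The variance of an arm mean is 1/26 + (7/33²)(25/26) = 0.0385 + 0.0062 = 0.0446, so the difference has SD √(2 × 0.0446) = 0.299.
- The reported error is 0.246/0.299 = 0.82 of the true one. A nominal 1.96 threshold is really 1.96 × 0.82 = 1.61, a two-sided error of about 0.11.

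**Step 3: simulation under no effect.** 33 per arm, 7 missing per arm, matching within arm on baseline, 5 donors, 3,000 replicates. The pooled analysis uses 10 imputations and Rubin's rules. All three analyses compare unadjusted means.

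| Correlation | Single fill: mean SE / true SD | Ratio | Type I error, single | Pooled | Complete case |
|---|---|---|---|---|---|
| 0 | 0.241 / 0.303 | 0.80 | 0.110 | 0.052 | 0.049 |
| 0.5 | 0.241 / 0.293 | 0.82 | 0.102 | 0.052 | 0.048 |
| 0.8 | 0.239 / 0.276 | 0.87 | 0.091 | 0.061 | 0.052 |

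The Monte Carlo error of a 5% rate is √(0.05 × 0.95/3000) = 0.004. The pooled 0.061 is therefore slightly above nominal, but well below the single fill.

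**Step 4: other set-ups.** A second simulation (6,000 runs per cell, single fill, t-test) gave 0.095, 0.076 and 0.067 at correlations 0.5, 0.7 and 0.85 with arm and baseline in the imputation model. With arm only it gave 0.114, 0.104 and 0.101. A further run at 33 per arm with 7 missing gave about 7-13% for a single fill, 5-6% pooled and 4-5% for complete cases. At 10% missing and correlation 0.7, the single-fill t-test gave 0.062.

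**Step 5: power.** At effect 0.8 and correlation 0.5, the single fill rejects in 0.845 of runs, pooled imputation in 0.819 and complete cases in 0.795. The single fill's apparent gain comes with an inflated error rate.

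**The case against.** The strongest reply is that the article never says that one dataset will be made or that filled values will be analysed as if observed. Predictive mean matching is a way of drawing imputed values, it is widely compatible with multiple imputation, and every imputation substitutes something. The number of imputations and the pooling rule are details that a condensed article often leaves to a fuller document. This stands in part: single imputation is the natural reading, not the only one, so the point must be conditional. It does not remove the point, because a stated rule gives wrong standard errors when followed as worded.

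Other objections also stand:

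- The 20% is a planning allowance, not a forecast. Sessions are held on school premises and absentees are contacted, so losses may be smaller.
- The 33 per arm, the missingness mechanism, the correlations and the donor count are assumptions.
- Complete-case analysis does well here partly because data were simulated as missing completely at random. That is no case for relying on it alone.

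A reader might also infer that the yoga effect will be pulled towards zero because arm is left out of the imputation model. In the worst case 0.8 would shrink to about 0.8 × 26/33 = 0.63 SD. The article does not say which variables enter the model, so this is a risk to exclude and not a fault of the plan.

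**Conclusion.** The point holds conditionally. If the rule is carried out in phase two as a single fill, the standard error is understated by about 13-20% and type I error is about 7-13% instead of 5%. This assumes 33 per arm, 7 missing per arm, data missing completely at random and a baseline correlation of 0 to 0.8. Multiple imputation with pooling brings the error to about 5-6%, so predictive mean matching itself is not the problem. With 10% missing the inflation is small (about 6%).

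Two stronger conclusions are not supported. The documents do not show that phase two inference is invalid, because they do not fix single imputation. Nor does the point reach every outcome in the study: the attrition allowance belongs to the three-month intervention, and phase one is a cross-sectional comparison without follow-up. Under the single-fill reading, though, the reassurance in Strengths and limitations ("though strategies such as imputation are planned to minimize their impact") would not hold for the error rate: in these simulations complete cases kept it and the fill did not.

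**What to change.** Replace the sentence with a rule for phase two along these lines:

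- **Imputation.** Missing post-assessment values are handled by multiple imputation using predictive mean matching, for example 20 or more imputations, with arm and the baseline outcome in the model. Age, sex and height may be added if the sample allows. With about 26 observed children per arm, the model must stay small. Leave out session attendance, because waitlist children have no yoga sessions before post-assessment.
- **Analysis.** Each completed dataset is analysed by ANCOVA adjusted for the baseline outcome, and results are pooled by Rubin's rules. Fixing this analysis in advance also removes the difficulty of pooling a rank-sum test or a test chosen on normality.
- **Sensitivity.** A complete-case ANCOVA is reported alongside.

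All the variables needed are already collected. The cost is revised wording, a little more analysis work and slightly wider intervals. In the simulation of unadjusted means, the pooled standard error was 5-12% larger than the single-fill one (0.251/0.239 = 1.05; 0.269/0.241 = 1.12). Pooled power was still about 0.82 at effect 0.8 and correlation 0.5.

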## Discussion

Yoga as an alternative therapy has shown promise in enhancing physical fitness, increasing PEFR value [19], normalizing breath rate [6], and reducing fear of falling among children with VI [29]. Additionally, previous studies have shown that yoga and corrective exercises can help improve hyperkyphosis in elderly individuals [30]. However, research on the effects of yoga specifically on lung function in children with VI remains limited. To our knowledge, this study represents a pioneering effort with a robust design aimed at investigating the lung function and various factors such as physical activity, posture, heart rate variability, muscle strength, and psychological parameters in children with and without VI. Additionally, it seeks to explore the potential effects of a yoga intervention on these parameters. Through a waitlist-controlled design, we ethically provide all participants access to the yoga intervention. The findings may support yoga as a feasible strategy to enhance overall health in children with VI. This allows us to assess its impact on lung function, physical activity, posture, heart rate variability, muscle strength, and psychological well-being.

Strengths and limitations

This study combines objective health measures, such as lung function, muscle strength, posture, and heart rate variability, with validated psychological assessments, providing a comprehensive evaluation of children’s health. The RCT design, including a waitlist control group, allows all participants to benefit from the yoga program while providing a rigorous and ethically responsible evaluation of its effects. Inclusion of both visually impaired and sighted children allows meaningful comparisons and identification of specific needs in the VI population. Additionally, the structured 12-week yoga intervention with standardized protocols supports reproducibility and potential scalability for rehabilitation programs. Despite the robust design, several limitations should be acknowledged. Key limitations of the study include the open trial design, which may introduce performance and reporting bias as participants are aware of group allocation and may respond in socially desirable ways, and observer bias as assessors cannot be fully blinded. Variations in social support among participants are not controlled for, which could influence outcomes. Dropouts and missing data may also affect internal validity, though strategies such as imputation are planned to minimize their impact. Although participants come from different regions of the state, the study is conducted at a single center, which may limit generalizability to other regions.

## Conclusions

This study aims to provide comprehensive insights into the lung function, physical fitness, posture, autonomic function, muscle strength, and psychological well-being of children with and without VI. It is designed to evaluate the effects of a 12-week yoga intervention on these outcomes among children with VI. The study is hypothesis-driven and will examine whether yoga-based intervention is feasible and associated with improvements in health-related outcomes. The results are expected to contribute to the existing evidence base and may help inform future rehabilitation research and program development for children with VI.
